#### Other outcome measures

Predictors of adherence to condom use, CIN2 regression, and HR-HPV-clearance based on data on sexual habits etc., as known from the questionnaire.

### Power calculation

Based on the literature [16, 17], we expect the regression rate in non-condom users to be around 22%, and regression in condom users to be 2.5 times larger. We expect the rate of condom use to be 60% in the intervention group, which gives an expected relative risk of 2.0 for the intervention group compared to the control group. With a power of 95% and a 0.05 significance level, we would need 140 women in each group.

### Data analysis plan

The relative regression rate (RRR) for CIN2 in the intention-to-treat analysis will be calculated as$$ \mathrm{RRR}=\frac{\left(\mathrm{number}<\mathrm{CIN}2\ \mathrm{at}\ \mathrm{follow}\hbox{-} \mathrm{up}\ \mathrm{in}\ \mathrm{in}\mathrm{tervention}\ \mathrm{group}\right)/\left(\mathrm{all}\ \mathrm{women}\ \mathrm{in}\ \mathrm{in}\mathrm{tervention}\ \mathrm{group}\right)}{\left(\mathrm{number}<\mathrm{CIN}2\ \mathrm{at}\ \mathrm{follow}\hbox{-} \mathrm{up}\ \mathrm{in}\ \mathrm{control}\ \mathrm{group}\right)/\left(\mathrm{all}\ \mathrm{women}\ \mathrm{in}\ \mathrm{control}\ \mathrm{group}\right)}. $$

The relative HPV-clearance rate (RCR) is calculated as$$ {\displaystyle \begin{array}{l}\mathrm{RCR}=\\ {}\frac{\left(1-\mathrm{number}\ \mathrm{HR}\hbox{-} \mathrm{HPV}+\mathrm{at}\ \mathrm{follow}\hbox{-} \mathrm{up}\ \mathrm{in}\ \mathrm{in}\mathrm{tervention}\ \mathrm{group}\right)/\left(\mathrm{number}\ \mathrm{HR}\hbox{-} \mathrm{HPV}+\mathrm{at}\ \mathrm{baseline}\ \mathrm{in}\ \mathrm{in}\mathrm{tervention}\ \mathrm{group}\right)}{\left(1-\mathrm{number}\ \mathrm{HR}\hbox{-} \mathrm{HPV}+\mathrm{at}\ \mathrm{follow}\hbox{-} \mathrm{up}\ \mathrm{in}\ \mathrm{control}\ \mathrm{group}\right)/\left(\mathrm{number}\ \mathrm{HR}\hbox{-} \mathrm{HPV}+\mathrm{at}\ \mathrm{baseline}\ \mathrm{in}\ \mathrm{control}\ \mathrm{group}\right)}.\end{array}} $$

These calculations are possible because we have a closed population, in which all women recruited are followed up for the entire observation period. Logistic regression will be used to analyze the questionnaire data as predictors of outcomes. SAS version 9.4 will be used for the analysis.

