#### Intervention group

Women in the intervention group are called by the project physician and informed about the project. They are advised always to use condoms during intercourse until the next follow-up visit with a gynecologist. If they have not been reached after two calls, a text message is sent. If they have not been reached after a further two calls and one text message, they are considered missing. Those contacted either consent or do not consent to participate verbally. Participant information and the informed consent form is sent to the home address of women who consent. Free condoms are sent to the woman once the signed informed consent form has been returned to the project physician. As a reminder about adherence, a text message is sent halfway through the intervention period. Participating women continue with their previous contraceptives if any. At the end of the intervention period, a questionnaire is sent by email. The questionnaire requests information on use of contraceptives, age at first intercourse, lifetime number of sexual partners, frequency of sexual intercourse, condom use in the intervention period, number of sexual partners in the intervention period, smoking, number and time of births and abortions, and HPV vaccination. The intention was to send the questionnaire to all women in the intervention group at the time of follow-up. However, the ethics committee of the Capital Region has stipulated that the questionnaire is sent only to women who have consented to condom use.

For women in the intervention group, their diagnosis at the follow-up visit with a gynecologist is retrieved from the pathology register [19]. For participating women, samples from both baseline and follow-up visits to a gynecologist are tested for HPV.

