#### Control group

Women in the control group are not contacted by the project physician and therefore, not given advice on condom use as a way to enhance regression of their cervical lesions. Otherwise, they are examined and treated in exactly the same way as women in the intervention group. The biopsy result from the follow-up visit at the gynecologist is retrieved from the pathology register.

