#### Secondary endpoint

The secondary endpoint is clearance of HR-HPV for women who consented to condom use, based on the baseline sample and the follow-up sample. Clearance is defined as having a HR-HPV type at the time of CIN2 diagnosis that is not present at the follow-up. Previous studies have showed that having HPV16 will decrease the chance of regression of a CIN lesion [20]. Therefore, the initial HPV status and phenotypes might influence the regression rate of cervical lesions.

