### Data sources

From the gynecologists, we will receive the name, date of birth, and phone number of women who have consented to be contacted. Every second week, we will receive a list from the pathology register [19] with new CIN2 diagnoses. Sample results from the follow-up visits as well as HPV status at baseline and follow-up will be retrieved from the pathology register. Data on adherence to condom use will be obtained from the questionnaires. All data will be linked via the women’s unique personal identification number. The Danish Data Inspective Agency has approved the handling and storage of data (SUND-2016-21). All study-related material will be stored safely. Personal information on the participants is stored in secure computer systems.

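### The HPV-clearance ratio uses two unpaired counts, so even with its bracket repaired it scores a baseline-positive woman without a follow-up HPV result as cleared

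*Protocol article*

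**What the plan says.** The Secondary endpoint section restricts the endpoint to consenting women and ties it to two samples: "The secondary endpoint is clearance of HR-HPV for women who consented to condom use, based on the baseline sample and the follow-up sample". It then defines the event: "Clearance is defined as having a HR-HPV type at the time of CIN2 diagnosis that is not present at the follow-up".

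The Data analysis plan gives a formula, introduced by "The relative HPV-clearance rate (RCR) is calculated as". For each group the printed term is one minus the number HR-HPV positive at follow-up, the whole divided by the number HR-HPV positive at baseline. The intervention term is divided by the control term. Below it stands the justification for both this formula and the regression formula: "These calculations are possible because we have a closed population, in which all women recruited are followed up for the entire observation period".

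Three other places describe where the HPV results come from:

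- Intervention group: "For participating women, samples from both baseline and follow-up visits to a gynecologist are tested for HPV".
- Control group: the only follow-up result named is histological: "The biopsy result from the follow-up visit at the gynecologist is retrieved from the pathology register".
- Data sources, with no group named: "Sample results from the follow-up visits as well as HPV status at baseline and follow-up will be retrieved from the pathology register".

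The article states no expected clearance rate, no expected clearance ratio and no expected fraction of missing HPV results.

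**The concern.** A clearance rate should be the number of women who cleared divided by the number in whom clearance could be observed. This formula never counts women who cleared. It infers them from the gap between two totals, and nothing restricts the totals to the same women.

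A woman positive at baseline whose follow-up sample is absent, untested or invalid adds one to the baseline count and nothing to the follow-up count. A woman who truly cleared does exactly the same, so the formula cannot tell them apart. Under the definition in the Secondary endpoint section, the first woman has no outcome at all.

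The regression formula in the same section works the other way. Its denominator is all women in the group, so a woman without a follow-up diagnosis adds nothing to the numerator and counts as not regressed. One woman who misses her follow-up visit would be a failure for the primary endpoint and a success for the secondary one.

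If clearance is reported only for women who agreed to use condoms, any such inflation would be read as a benefit of condoms. If it is reported as a ratio of two groups, a difference in the availability of results could look like a treatment effect.

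**Working it through.** **Inputs.** The formula, the definition of clearance and the statement of complete follow-up come from the article. There is no clearance figure in the plan to reproduce. Every clearance rate c, missing fraction m and count below is an assumption chosen for illustration.

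**Step 1: the term as printed.** Take B = 100 baseline positives per group, no missing results, and true clearance of 40% (intervention) and 20% (control), so F = 60 and F = 80.

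- Intervention: (1 − 60)/100 = −0.59
- Control: (1 − 80)/100 = −0.79
- Ratio: 0.59/0.79 = 0.75, where the true ratio is 0.40/0.20 = 2.00

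The term is negative once two or more women are positive at follow-up. The intended form must be 1 − F/B = (B − F)/B, which gives 0.40 and 0.20 and a ratio of 2.00.

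**Step 2: the intended term with missing results.** Let a fraction m of baseline positives have no valid follow-up result, let clearance among the rest be c, and let there be no new positives. Then F = B(1 − m)(1 − c), and

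apparent clearance = 1 − (1 − m)(1 − c) = c + m(1 − c).

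If results are missing at random, c is also the true clearance and the excess is m(1 − c).

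| c | m = 0 | m = 5% | m = 10% | m = 20% |
|---|---|---|---|---|
| 30% | 30.0% | 33.5% | 37.0% | 44.0% |
| 40% | 40.0% | 43.0% | 46.0% | 52.0% |

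**Step 3: a worked record.** Of 80 women positive at baseline, 8 have no follow-up result and 50 of the other 72 are still positive.

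- Intended formula: 1 − 50/80 = 37.5%
- Paired count: 22/72 = 30.6%
- Missing counted as not cleared: 22/80 = 27.5%

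**Step 4: new positives.** F is a count of all women HR-HPV positive at follow-up. It therefore also includes women negative at baseline who became positive, and women who lost one type and gained another. If six such women are added to the record in Step 3, the formula gives 1 − 56/80 = 30.0%, and the excess is cancelled.

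**Step 5: the ratio of two groups** (intended form, no new positives, missing at random).

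| True clearance, intervention vs control | Missing, intervention vs control | Apparent clearance | Ratio | True ratio |
|---|---|---|---|---|
| 30% vs 30% | 10% vs 10% | 37.0% vs 37.0% | 1.00 | 1.00 |
| 30% vs 30% | 15% vs 5% | 40.5% vs 33.5% | 1.21 | 1.00 |
| 30% vs 30% | 5% vs 15% | 33.5% vs 40.5% | 0.83 | 1.00 |
| 40% vs 20% | 10% vs 10% | 46% vs 28% | 1.64 | 2.00 |
| 40% vs 20% | 20% vs 5% | 52% vs 24% | 2.17 | 2.00 |
| 40% vs 20% | 5% vs 20% | 43% vs 36% | 1.19 | 2.00 |

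Equal missingness leaves a null ratio alone and pulls a real effect towards 1. Unequal missingness can move the ratio either way.

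**The case against.** **Complete follow-up is stated.** The sentence directly under the formulas says that every recruited woman is followed throughout. With no missing results the excess is zero. Nor does the drop-out paragraph under Strengths and limitations supply a rate: its examples are women who gave no permission for contact, were not reached or declined, not participants whose second HPV result is lacking. This stands, and it makes the size of the error unknown. It does not remove the error. Following a woman is not the same as having a valid HPV result for her. The primary endpoint needs only a biopsy diagnosis, whereas clearance needs a second HPV test, and the article describes that testing for participating women and names only a biopsy result for controls.

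**The printed formula does something else.** A reader might infer that the plan subtracts follow-up positives from baseline positives. It does not: it subtracts a count from one. This also stands, so the scoring error belongs to the repaired formula. But moving the bracket alone would leave that error in place, because the two counts would still be unpaired.

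**The net direction is open.** A reader might infer that clearance will be overstated, or that the ratio will favour condoms. The documents support neither. New positives lower apparent clearance, and the ratio has no fixed direction of error. It is not even clear that the control term can be computed.

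**Missing-data rules belong in a fuller document.** In general they do, and silence would be no fault. Here the article is not silent: it fixes a formula that gives women without a result a favourable outcome, against its own definition.

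**Conclusion.** The point holds in a limited form. The stated formula is not a proportion as printed. In its evident intent it does not implement the article's definition of clearance: a baseline-positive woman without a valid follow-up HPV result is scored as cleared, whereas the regression formula scores an absent result as a failure. The only protection is an assertion of complete follow-up, which does not guarantee a second HPV result for each woman.

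The size cannot be fixed from the article. At an assumed clearance of 30%, the excess is 3.5, 7 and 14 percentage points for 5%, 10% and 20% missing, provided that results are missing at random and there are no new positives. It is nil if nothing is missing. The documents do not show that the trial's reported clearance will be too high or that the between-group ratio will be biased in a known direction. The formula should be corrected before the secondary endpoint is analysed; the primary endpoint is not affected.

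**What to change.** Replace the formula with a paired count:

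- **Denominator:** women HR-HPV positive at baseline who have a valid follow-up HPV result.
- **Numerator:** those among them whose baseline HR-HPV type is absent at follow-up, as the Secondary endpoint section defines it.
- **Reporting:** give the number of baseline-positive women without a valid follow-up result, by group where it applies.
- **Sensitivity analysis:** one, counting those women as not cleared, which is the direction the regression formula already takes.
- **Ratio:** compute a between-group ratio only if HPV results exist for the control group. Otherwise report clearance in the consenting women alone and drop the ratio.

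The paired count also removes the misplaced bracket and the offset from new positives. The cost is one reworded formula and one extra line of analysis, with no new data. The denominator may be slightly smaller and the clearance figure less favourable. With complete results, the pairing excludes no baseline-positive woman.

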### Strengths and limitations

A strength of this study is its design as a public health randomized controlled trial embedded in the routine treatment and follow-up program for women with cervical lesions. This gives us two groups of women who are comparable except for the intervention. It is, furthermore, a strength to have three regions included. In Denmark, health care is paid for by the government and is free of charge [26], but there are minor regional variations in clinical procedures, and recruiting participants from three regions ensures that there is a representative sample of women.

The number of drop-outs is a limitation in this project. We do not receive consent to be contacted from all women attending a gynecologist, some women in the intervention group cannot be reached by phone or text message, and some women do not want to participate. Participating women may, therefore, be a selected group. Furthermore, adherence to condom use is inevitably self-reported. This information is collected from questionnaires at the end of the project, so there could be some recall bias. A punch biopsy may alter the HPV infection, and the disappearance of a type-specific HPV infection can be caused either by a biopsy or by an actual clearance. As the study is embedded in the clinical setting, we are not able to validate histology diagnoses or perform p16 staining. However, as the routine diagnostic procedures are used for both the intervention group and the control group, any possible misclassification will affect the two groups equally.

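### The primary regression ratio assumes complete follow-up, so a woman without a follow-up biopsy is counted by default as not regressed; this can bias the ratio in either direction if biopsy rates differ by arm

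*Protocol article*

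**What the plan says.** The Data analysis plan of the protocol article writes out the intention-to-treat relative regression rate (RRR). In each arm it is the number below CIN2 at follow-up divided by all women in that arm, and the intervention proportion is divided by the control proportion. The calculation is said to be possible because "we have a closed population, in which all women recruited are followed up for the entire observation period".

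Other sections bear on this:
- Target population: a woman enters if a 6-month examination has been scheduled. Attendance is not, and could not be, an entry condition.
- Primary endpoint: regression is a diagnosis below CIN2 in the follow-up biopsy.
- Intervention group, Control group and Data sources: follow-up results are retrieved from the pathology register in both arms.
- Power calculation: 140 women per group, with no allowance for absent outcomes.
- Blinding: the trial is open. Intervention women are telephoned, and those who consent also receive mailings and a text ("As a reminder about adherence, a text message is sent halfway through the intervention period"). By contrast, "Women in the control group are not contacted by the project physician".
- Trial status: the last follow-up diagnoses were still to come, so complete follow-up was assumed and not yet observed.

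**The concern.** A pathology register can return only the biopsies that were taken. A woman who misses the visit, or attends without a biopsy, has no follow-up histology. Under the fixed formula she is a non-regressor. That value is not chosen and defended as a missing-data rule. It follows by default from the premise that nothing will be missing.

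If the proportion without a biopsy differs between arms, the primary ratio mixes regression with attendance. The arms are handled differently and openly, so equal attendance cannot be taken for granted. If the proportion is the same, the ratio is unaffected, but the trial has less power than stated.

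**Working it through.** **Inputs from the Power calculation**
- Control regression: "we expect the regression rate in non-condom users to be around 22" per cent, so 0.22.
- Condom users: "regression in condom users to be 2.5 times larger", so 2.5 × 0.22 = 0.55.
- Uptake: "We expect the rate of condom use to be 60% in the intervention group".
- Intervention arm: 0.6 × 0.55 + 0.4 × 0.22 = 0.418, a ratio of 0.418/0.22 = 1.90. The article states an "expected relative risk of 2.0 for the intervention group compared to the control group"; that difference is a separate matter.
- 140 per arm, significance level 0.05 (taken as two-sided), power 95%.

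**Assumed:** the proportion without a follow-up biopsy, m_I (intervention) and m_C (control), between 0 and 20%. The article gives no figure. Absentees are assumed to regress at the same rate as attenders in their arm.

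**Step 1: the plan's own figure.** The pooled-variance formula for two proportions, 0.22 vs 0.418, without continuity correction, gives 142 per arm. At 140 per arm the power is 94.9%. So 140 is reproduced closely, with complete follow-up and no margin. With 0.44 (a ratio of 2.0) the same formula gives 116, so 0.418 is the better basis for the checks below.

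**Step 2: effect on the ratio.** The expected proportion counted as regressed is p(1 − m), so

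expected RRR = true RR × (1 − m_I)/(1 − m_C).

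| m_I / m_C | Factor | Null RRR | True 1.90 becomes |
|---|---|---|---|
| 5% / 10% | 0.95/0.90 = 1.056 | 1.06 | 2.01 |
| 10% / 20% | 0.90/0.80 = 1.125 | 1.13 | 2.14 |
| 10% / 5% | 0.90/0.95 = 0.947 | 0.95 | 1.80 |
| 20% / 10% | 0.80/0.90 = 0.889 | 0.89 | 1.69 |

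**Step 3: false-positive rate with no true effect.** Put a = p(1 − m_I), b = p(1 − m_C), d = a − b, n = 140. SE0 is the pooled standard error and SE1 the unpooled one. The rejection rate is Φ((d − 1.96·SE0)/SE1) + Φ((−d − 1.96·SE0)/SE1). The base rates are 22% (Power calculation) and 35% (non-condom users in the earlier randomised trial cited in the Discussion).

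| m_I / m_C | p = 0.22 | p = 0.35 |
|---|---|---|
| 5% / 10% | 5.6% | 6.1% |
| 10% / 20% | 7.6% | 9.8% |

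Example: for p = 0.22 at 10%/20%, a = 0.198, b = 0.176, d = 0.022 and both standard errors are 0.0466, which gives 7.6%.

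**Step 4: power with equal loss, 0.418 vs 0.22, 140 randomised per arm.**

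| Loss in each arm | Missing = not regressed | Biopsied women only |
|---|---|---|
| 0% | 94.9% | 94.9% |
| 10% | 91.3% | 92.6% |
| 20% | 86.4% | 89.4% |

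The ratio stays at 1.90 throughout. At 10% loss the denominator accounts for 92.6 − 91.3 = 1.3 points, and at 20% for 89.4 − 86.4 = 3.0 points. The rest comes from the outcomes being absent.

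With unequal loss of 20%/10%, power under the fixed formula falls to 73.6%. With 5%/10% the chance of rejection rises to 95.8%, but that is upward bias and not valid power.

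**The case against.** The case against has several parts, and much of it stands.

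- **Loss may be small.** The register covers both arms and captures every biopsy taken, every woman has a visit booked, and controls are otherwise managed in the same way. This stands: the article does not show that biopsies will be missing, or by how much.
- **The limitations section may seem to contradict the closed-population claim.** It says "The number of drop-outs is a limitation in this project". But the women it describes gave no consent to contact, could not be reached, or declined. The first group is never randomised, and for the others the diagnosis is still retrieved from the register. This is drop-out from recruitment or intervention, not demonstrated loss of the primary outcome.
- **A reader might infer bias in favour of condoms**, because intervention women are contacted and condoms prevent pregnancy. The documents do not support this. The text message is a reminder about adherence, not about the visit. The mailings go only to consenting women. The wish to conceive is a future one, participants keep their previous contraceptives, and no rule links pregnancy to omission of the biopsy. Different contact by arm is a reason not to assume equal attendance; it does not settle the direction.
- **An all-randomised denominator with missing counted as failure is a recognised convention.** True, and it can stay as one analysis. For a woman treated before follow-up, non-regression may even be a sensible value. But here the convention rests on a claim of no missing data.
- **Missing-data methods belong in the analysis plan.** Generally so, and their absence from an article would be no finding. This article, however, fixes the formula and states the premise itself.

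**Conclusion.** The point holds as a conditional one. The primary ratio rests on an assertion of complete follow-up that the design does not secure, and the formula turns any absent biopsy into a non-regression. The resulting bias can go either way. With differences of 5 to 10 percentage points in loss, a null ratio moves to between 0.89 and 1.13. When the control arm has the greater loss, the false-positive rate is 5.6% to 9.8% for base rates of 22% to 35%. A true 1.90 could appear as anything from 1.69 to 2.14.

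Equal loss does not bias the ratio. It lowers power from 95% to 91% at 10% loss and 86% at 20%, and only about 1 to 3 points of that are due to the denominator. It would be wrong to conclude that the denominator itself makes the trial underpowered. At the article's rounded ratio of 2.0, power at 10% equal loss is still 95.6%.

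All of these sizes depend on assumed loss rates and on absentees regressing like attenders in their arm. A demonstrated bias towards the intervention is not shown.

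**What to change.** 1. Delete the closed-population sentence, and state that a woman without follow-up histology has a missing primary outcome.
2. Report by arm the number of women without a follow-up biopsy and the reason.
3. Keep the all-randomised ratio, labelled as counting missing as not regressed. Present it together with a prespecified complete-case analysis and a tipping-point analysis that varies the regression rate among absentees separately in each arm.
4. Multiple imputation by arm, region and age is optional. It assumes that outcomes are missing at random given those variables, which is doubtful for women treated before follow-up; they should be considered separately.
5. Claim an effect only if it is robust across these analyses.
6. State that the 95% power assumes complete follow-up. For scale, restoring 95% power at 10% loss would take 140/0.90 = 156 women per arm if absentees are excluded, or 165 if they count as not regressed. Recruitment has closed, so this is a matter of honest statement, not of adding women.

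The cost is a little extra programming, recording reasons where they can be obtained, and a less favourable stated power. The biopsy counts need no source beyond the register.
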